### Primary Outcome Measurement

The fMRI examination will be performed in the Imaging Department of the Rehabilitation Hospital affiliated to Fujian University of Traditional Chinese Medicine. The first fMRI scan will be performed 1 day before the start of treatment, and the second fMRI scan will be performed within 6 hours after the last intervention. The fMRI data will be collected by a 3.0 Tesla magnetic resonance scanner (MAGNETOM Prisma 3.0T, Siemens) with 64-channel phase-array head coils. During the acquisition process, participants will be required to close their eyes, relax, stay awake, keep their heads fixed as far as possible, and not perform thinking activities. We will perform fMRI at the beginning and end of the experiment.

To acquire the structural images, we will use the following parameters. The T1-weighted imaging scan parameters are as follows: time of repeat=2200 ms, time of echo=2.48 ms, flip angle=8°, field of view=230 mm×230 mm, matrix=256×256, resolution=0.98×0.98×1 mm^3^, slice number=160, and slice thickness=1.0 mm. The functional images will be acquired using the following parameters: time of repeat=2000 ms, time of echo=30 ms, flip angle=90°, field of view=230 mm, matrix=64×64, resolution=3.6×3.6×3.6 mm^3^, slice number=37, slice thickness=3.6 mm, and scan time=10 minutes for 300 timepoints.

### Secondary Outcome Measurements

#### SF-MPQ Indicators

We will translate the SF-MPQ into Chinese to assess pain perception. This questionnaire consists of 5 indicators [22]: sensory pain rating index, affective pain rating index, total pain rating index, visual analog scale (which assesses the overall intensity of the total pain experience), and present pain index. The sensory pain rating index consists of 11 items describing sensory pain, and the affective pain rating index consists of 4 items describing emotional pain, with scores of 0 (none), 1 (mild), 2 (moderate), and 3 (severe). The total pain rating index is the sum of the sensory pain rating index and affective pain rating index. The overall intensity assessment of total pain experience consists of a visual analog scale ranging from 0 to 10, with 0 indicating no pain and 10 indicating the most severe pain imaginable [23]. In addition, 6 levels appear in the present pain index to describe the patient’s pain level: no pain, mild, uncomfortable, painful, terrible, and unbearable expressed as 0, 1, 2, 3, 4, and 5 points, respectively, for each participant. We will ask participants to indicate the score that best matches their level of pain.

#### PPT Test

PPT is a quantitative sensory test that can effectively describe the intensity of pain [24]. When the patient lies in the prone position, the estimator first locates the Dachangshu (BL25), Guanyuanshu (BL26), and Xiaochangshu (BL27) on the patient’s erector spinae muscles and Zhibian (BL54) and Huantiao (GB30) on the gluteus maximus muscles and uses them as test points (Figure 4). Then, the estimator will use the handheld tenderness tester (FTX50, Wagner) to press the test points at a uniform speed, lock it immediately when the patient feels pain, and then record the pressure value. The PPT will be measured every 5 minutes; a total of 3 measurements will be recorded, and the average will be taken to indicate the PPTs.

**Figure 4 figure4:**
[figure not shown]
Test points used to measure the pressure pain threshold. BL25: Dachangshu; BL26: Guanyuanshu; BL27: Xiaochangshu; BL54: Zhibian; GB30: Huantiao.

#### ODI Questionnaire

The ODI is a commonly used questionnaire for self-quantification of dysfunction in patients with LDH, and it has good reliability and sensitivity in patients with LDH [25]. This questionnaire consists of 10 questions. The score for each question ranges from 0 to 5. The maximum total score is 45 points. ODI score = [actual score/(5×number of actual answered questions)]×100%. The higher the score, the more severe the dysfunction.

#### Safety Evaluation

The investigators will assess the adverse events, defined as unexpected or adverse reactions occurring during or after treatment. In this experiment, adverse events [26] will be defined as (1) syncope, (2) ecchymosis, (3) increased pain, (4) fracture, and (5) skin allergy. The investigator will assess and solve the adverse events during the study, reporting them to the appropriate departments and ethics committees. Following that, they will monitor all the adverse events until the event resolves or the participant’s condition becomes chronic or stable, and they will make every effort to ensure their safety and record the relevant information in case report forms.

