### Exclusion Criteria

The exclusion criteria are as follows: (1) patients with progressive neurological deficit or cauda equina syndrome; (2) patients with LDH combined with other major lumbar diseases such as tumor, tuberculosis, and severe osteoporosis; (3) patients with trauma, acute lumbar injury caused by surgery pain, and lower limb nerve injury; (4) patients with any other condition causing lower limb neuropathy (diabetes or neurological diseases); (5) patients with cardiovascular, pulmonary, renal, hematopoietic system, and other major diseases; (6) patients with mental health issues; (7) pregnant or lactating women; and (8) patients with contraindications for fMRI.

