### Comprehensive Suspension Criteria

The comprehensive suspension criteria are as follows: (1) participants in the study have serious adverse effects due to a poor treatment plan, (2) participants experience severe complications or disease deterioration during the study period, and (3) if the test termination conditions are met after the doctor follows the standard operating procedure treatment, they shall be terminated immediately.

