#### Quality Control of the Research Participants

Before the study begins, we will provide each participant with details about the operability and precautions of the intervention method, prohibit other treatment methods during the intervention, and provide free health counseling throughout the study. With the informed consent of the participants, the corresponding test contents can be included and conducted voluntarily. If the pain fails to be relieved during the intervention, the project team must be informed in time and relevant drugs must be given if necessary; if the symptoms cannot be relieved, comprehensive treatment should be given immediately. If there is an accident or adverse event during a treatment event, the record form should be filled accurately, providing details such as the adverse event type, occurrence time, severity, duration, measures taken, and other reports.

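### The Safety Evaluation section defines adverse events twice, once openly and once as a closed list of five, and does not say which definition governs

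*Protocol article*

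**What the plan says.** The Safety Evaluation section opens with a general definition: "The investigators will assess the adverse events, defined as unexpected or adverse reactions occurring during or after treatment". It then gives a second one for this trial: "In this experiment, adverse events [26] will be defined as (1) syncope, (2) ecchymosis, (3) increased pain, (4) fracture, and (5) skin allergy". The duties that follow (assessment, reporting to the relevant departments and ethics committees, monitoring, and entry in the case report form) all attach to adverse events as a class. For monitoring, the text reads "they will monitor all the adverse events until the event resolves or the participant’s condition becomes chronic or stable".

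Three other places bear on the scope:

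- **Comprehensive Suspension Criteria.** These include "participants in the study have serious adverse effects due to a poor treatment plan" and "participants experience severe complications or disease deterioration during the study period". Neither is tied to the five items.
- **Quality Control of the Research Participants.** "If there is an accident or adverse event during a treatment event, the record form should be filled accurately", with the type and severity of the event among the details to be given. No limit to five types is stated.
- **Exclusion Criteria.** "patients with progressive neurological deficit or cauda equina syndrome" are not eligible. This is the only place where neurological deficit of this kind is named, and it concerns entry to the trial, not events during it.

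The Follow-Up section says that the 1-month follow-up serves to evaluate efficacy and safety. The telephone call it describes asks about recurrence of symptoms.

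**The concern.** A safety comparison between two arms depends on one definition applied in the same way to every participant. Here two neighbouring sentences give definitions of different breadth. A recorder who follows the first would enter any adverse or unexpected reaction. A recorder who follows the second would enter only five kinds of event.

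The difference matters for this population. Participants have a herniated disc at L4-L5 or L5-S1 with nerve root pain. They receive either Tuina, which includes an oblique pull of the lumbar region, or TENS with traction. The trial already treats progressive neurological deficit as important enough to bar entry, yet the list of on-study events does not contain it. Therapists and patients know the allocation, so if the choice of definition is left to judgement, recording could differ between the arms for reasons unrelated to true harm.

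**Working it through.** No arithmetic applies. The article states no adverse event rate, safety sample size or safety threshold. The check is to read the passages against each other.

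**Step 1: is the second definition closed?** It says what adverse events will be defined as in this experiment and then numbers five items. It contains no expression that marks them as examples, and no sixth category for anything else. On its own terms it is closed.

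**Step 2: is precedence stated?** No. The ordinary reading is that a specific sentence narrows a general one that precedes it. It is also possible to read the pair as a general definition followed by the events expected in this trial. The text does not choose between them.

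**Step 3: put example events through each provision.**

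| Event | Open definition | Five-item list | Suspension criteria | Quality control record form |
|---|---|---|---|---|
| Ecchymosis | Yes | Yes | Only if serious or severe | Yes, if during a treatment event |
| Worsening leg pain | Yes | Yes, as increased pain | If it amounts to deterioration | Yes, if during a treatment event |
| New weakness without more pain | Yes, as an unexpected or adverse reaction | No | If a severe complication or deterioration | Possibly, if during a treatment event |
| New sphincter symptoms without more pain | Yes, as an unexpected or adverse reaction | No | If a severe complication or deterioration | Possibly, if during a treatment event |

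The two definitions agree on the first two rows and disagree on the last two.

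**Step 4: do the other provisions settle the disagreement?** Only in part.

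- The suspension criteria say when participation is to be suspended. They do not define an adverse event and carry no reporting duty of their own.
- The record form covers accidents as well as adverse events and does not restrict types. For anything that is not an accident, however, it still relies on the meaning of adverse event. Its wording also concerns events during a treatment event, so harm that appears later is not clearly covered.
- The Data Collection and Monitoring section puts adverse events in the case report form, again without saying which definition applies.
- The Dropout Criteria count as a dropout a participant who has an accident during treatment and cannot continue. A harm outside the list could be entered under that heading instead of as an adverse event.
- The 1-month call, as described, asks about symptom recurrence. Participants may also report symptoms by other routes, but no specific enquiry about adverse events is described.

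**The case against.** The strongest case on the other side has four parts.

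1. **The open sentence comes first and nothing revokes it.** New weakness after treatment fits it, so one cannot say that such an event falls outside the trial's definition. This stands. It is why the point is an inconsistency and not a plain exclusion.
2. **Other sections catch serious harm.** The suspension criteria and the record form are not limited to five items, and increased pain, which is on the list, would capture deterioration that shows itself as pain. This stands as mitigation. It does not say which definition controls reporting to the ethics committee, monitoring to resolution or the comparison between arms.
3. **This is a journal article, and the list cites a source that is not at hand.** The full protocol or the case report form may present the five items as expected events only. That is possible. But the conflict lies between two sentences that are both printed here, so it is not a detail merely left to a fuller document.
4. **Nothing in the article says that either treatment causes neurological deficit.** This is also right. The exclusion criterion shows only that the protocol regards the condition as important at entry. The deficit serves here as an example of an event on which the two definitions disagree, with no claim about how often it occurs.

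A reader might infer from the list that neurological or other off-list harm would go unrecorded. The documents do not support that, because the open sentence, the suspension criteria and the record form each give a route by which it could be captured.

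**Conclusion.** The inconsistency is real and should be corrected. The section gives an open definition and a closed one without stating precedence. If the closed one governs, events outside the five items need not be reported, monitored or compared as adverse events. If the open one governs, they are covered and the list only needs relabelling.

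The size of the effect on the safety results cannot be derived from the article. A confidence bound for zero observed events would not supply it, since such a bound assumes complete ascertainment and does not measure what a definition leaves out.

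The conclusion rests on the printed wording alone. It assumes that the full protocol and case report form, which are not shown, do not already resolve the conflict. The primary fMRI analysis and the efficacy outcomes are not affected.

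**What to change.** Reconcile the two sentences with each other, and with the suspension criteria and the quality control text. Wording along these lines would do it:

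> The general definition in this section applies in both arms from the first treatment session to the 1-month follow-up. A new or worsening neurological deficit falls under it. Syncope, ecchymosis, increased pain, fracture and skin allergy are expected events that are asked about specifically. An event not named here is recorded, reported and followed in the same way.

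Two consequential edits follow. The quality control text should refer to this definition, and the 1-month call should include a question about adverse events. The article should also make clear that a harm meeting a suspension criterion is recorded as an adverse event. This leaves the suspension criteria themselves unchanged.

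The cost is a change to protocol and case report form wording and slightly more recording work. Data from 21 cases had been collected by July 1, 2024, so the amendment should give the date from which the clarified definition was applied.

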#### Follow-Up

To evaluate the efficacy and safety of the intervention, we will follow up with the participants for 1 month after the end of the treatment. A month after the treatment ends, the results evaluator will call the participants to investigate the recurrence of their symptoms. Participants can also inform evaluators of their clinical symptoms face-to-face or via email, text message, or WeChat at the relevant timepoint.

#### Data Collection and Monitoring

The outcome assessors will record the detailed information in case report forms, including the evaluation of treatment effectiveness, adverse events, questionnaire data, and fMRI data. Two data administrators outside the team will use the Excel database for data entry and management, and these data administrators must complete rigorous training in data monitoring. To ensure the accuracy of the data, 2 data administrators will enter the information independently and proofread it, and they will enter the real-time data into the China Clinical Trial Registration Center. During the trial, the Rehabilitation Hospital affiliated to Fujian University of Traditional Chinese Medicine will review the conduct of the trial.

### fMRI Data Preprocessing

First, MRIConvert 2.0 software (Lewis Center for Neuroimaging) converts the DICOM format of the fMRI images into a Neuroimaging Informatics Technology Initiative format file for data analysis. Next, we apply the default preprocessing pipeline in the Statistical Parametric Mapping–based CONN 2.0b toolbox of the MATLAB 2022b (The MathWorks, Inc) platform to preprocess all the nuclear magnetic data.

### fMRI Data Processing

#### ALFF Analysis

The ALFF analysis will be performed using the AFNI (Analysis of Functional NeuroImages) software [27]. The fast Fourier transform transforms the filtered time series to the frequency domain (parameters: taper=0%, fast Fourier transform length=shortest) to obtain the power spectrum. Since the power of a given frequency is proportional to the square of the magnitude of this frequency component in the original time series, the square root is calculated at each frequency of the power spectrum, and the average square root ranges from 0.01 Hz to 0.08 Hz at each voxel. This average square root is considered as the ALFF.

#### ReHo Analysis

The Kendall coefficient of concordance is used to measure the local synchronization of the time series of its nearest neighbor voxels as 
[figure not shown]

[28], where W is the Kendall coefficient of concordance among given voxels, ranging from 0 to 1; Ri is the sum rank of the ith timepoint; R (n+1) K/2 is the mean of Ri; K is the number of time series within a measured cluster (K=7, 19, and 27; K=27 is used in this study); and n is the number of ranks (here n=60). The Kendall coefficient of concordance program is coded in MATLAB [29]. Thus, an individual ReHo map is generated for each data set.

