#### FC Analysis

Differential brain regions obtained by ALFF or ReHo analysis, regions of interest, and differential brain regions will be selected, and FC will be calculated. An FC plot for each participant will be obtained by DynamicBC using the sliding window method. We will select a window length of 50 times of repeat (time of repeat: 100 seconds) with a window overlap of 98% (step size of 1 time of repeat) to calculate the FC for each participant. The FC plots for each participant will be calculated within each window to generate a series of FC plots. The coefficient of variation of the FC map is calculated to measure the temporal variability of intrinsic brain activity. Finally, the FC variability of all the participants will be transformed into standardized *z* scores to enhance the normality of the data by subtracting the mean of each voxel and dividing by the standard deviation [30].

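### The ReHo formula sets n=60, but n counts timepoints and the functional scan has 300; the text needs correcting and the program checking

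*Protocol article*

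**What the plan says.** Under ReHo Analysis, local synchronization is measured by Kendall's coefficient of concordance W, said to lie between 0 and 1. The section defines its symbols: "Ri is the sum rank of the ith timepoint", the mean of the Ri is (n+1)K/2, "K=27 is used in this study", and "n is the number of ranks (here n=60" (the bracket closes there). It adds that the program is written in MATLAB, with a citation, and closes: "Thus, an individual ReHo map is generated for each data set".

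Under Primary Outcome Measurement the acquisition is fixed: "The functional images will be acquired using the following parameters: time of repeat=2000 ms", and later in the same list "scan time=10 minutes for 300 timepoints".

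Two other places could bear on n. fMRI Data Preprocessing says only that "we apply the default preprocessing pipeline in the Statistical Parametric Mapping–based CONN 2.0b toolbox", after a file-format conversion. FC Analysis uses a sliding window: "We will select a window length of 50 times of repeat (time of repeat: 100 seconds".

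**The concern.** The value 60 is given as this trial's own setting, beside K=27, yet the trial's scan yields 300 timepoints. fMRI is the main outcome, ReHo is one of the two measures named for the t test in Statistical Analysis, and regions found by ALFF or ReHo are carried into the FC analysis. An error in how W is computed could therefore reach beyond the ReHo maps.

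Two things could go wrong if 60 is taken literally. The constant could be put into the formula while 300 points are ranked, which gives impossible values of W. Or the series could be shortened to 60 volumes to match the text, which discards most of each scan. A third possibility is harmless: the program counts the timepoints itself and only the description is wrong.

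**Working it through.** **1. Reproduce the scan length.** Scan time 10 min = 600 s; repetition time 2000 ms = 2 s. 600 / 2 = 300, which agrees with the article's 300 timepoints. The FC window also agrees with a 2 s repetition time: 50 × 2 s = 100 s.

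**2. Identify n.** Ri is the rank sum at timepoint i, and the mean of the Ri is (n+1)K/2. That mean is correct only if each of the K series is ranked from 1 to n over its timepoints. So n is the number of timepoints.

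**3. Try to obtain 60.**
- 60 volumes at 2 s last 120 s, one fifth of 600 s.
- 60 volumes in 600 s would need a repetition time of 10 s.
- The only window is 50 repetitions, not 60, and it belongs to FC. ReHo gives one map per data set.
- No removal of volumes down to 60 is described in preprocessing.

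None of these gives 60.

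**4. Effect if 60 is put into the formula for 300-point series.** The formula image is not shown, so I assume the standard form, which fits the symbols defined:

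W = [ΣRi² − n·R̄²] / [K²(n³ − n)/12], with R̄ = (n+1)K/2 and K = 27.

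- With n = 300: R̄ = 301 × 27/2 = 4063.5. With n = 60: R̄ = 61 × 27/2 = 823.5.
- Ratio of denominators: b = (300³ − 300)/(60³ − 60) = 26,999,700/215,940 = 125.03.
- Shift from the wrong mean term: a = (300 × 4063.5² − 60 × 823.5²)/(27² × 215,940/12) = 4,912,920,540/13,118,355 = 374.5.
- So the miscomputed value is W′ = 374.5 + 125.03 W. If only the denominator is wrong, W′ = 125.03 W.

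Because a and b depend only on K and on the two values of n, they are the same at every voxel, participant and visit when all scans have the same length. With b > 0, a t statistic on W′ equals that on W.

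**5. Effect if the series is cut to 60 volumes.** Simulation, 400 runs per setting, K = 27, independent timepoints, within-cluster correlation ρ assumed:

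| ρ | W, n=300: mean (SD) | W, 60 volumes: mean (SD) | SD ratio | 60 in full formula, 300 points: mean | 60 in denominator only: mean |
|---|---|---|---|---|---|
| 0 | 0.037 (0.0028) | 0.037 (0.0066) | 2.4 | 379.1 | 4.6 |
| 0.2 | 0.221 (0.0150) | 0.221 (0.0327) | 2.2 | 402.1 | 27.6 |
| 0.5 | 0.500 (0.0222) | 0.492 (0.0511) | 2.3 | 437.0 | 62.5 |

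The SD ratios lie near √(300/60) = √5 = 2.24. The simulated means with 60 in the full formula agree with step 4: for example 374.5 + 125.03 × 0.500 = 437.0.

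**The case against.** The mismatch itself is hard to dispute; the objection is to its importance.

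First, a reader might infer that ReHo must be either wrongly normalised or computed from one fifth of the data. The article does not support that. It says only that the program is coded in MATLAB and cites a source; it does not say that 60 is hard-coded. The number may have been carried over from where the formula was taken, with the program reading n from the data. Then the analysis is unaffected. This stands.

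Second, values of W near 400 look alarming but would not distort the group comparison: the rescaling in step 4 cancels from every t test when scans are equally long. Such values would also be obvious against a range of 0 to 1. This stands too, provided W is tested on its own scale, and the article describes no other scaling of the ReHo maps.

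Third, truncation is the only reading that costs information, and no section states it. The roughly 2.2-fold figure is a within-scan sampling SD under assumed correlations and independent timepoints. The group test also carries variation between participants, so the loss at trial level would be smaller than that factor, and no loss of power is shown. This stands.

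Fourth, ReHo is not named as the primary endpoint. The article makes fMRI as a whole the main measurement, with ALFF, ReHo and FC beneath it. This also stands.

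What the objection does not do is explain 60. The article gives the parameter and gives it inconsistently, so this is not detail left to a fuller document. Nor does the article let a reader tell which of the three readings applies.

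**Conclusion.** The point holds as an error in a stated analysis parameter for one of the main fMRI measures: n is given as 60 where the trial's own acquisition gives 300, less any initial volumes discarded. The mismatch rests on the article's own definitions and on 600 s / 2 s, with no outside assumption.

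The consequence is open:
- **Program reads n from the data:** no effect beyond the text.
- **60 used in the formula on 300 points:** reported W is invalid (a factor of 125.03, plus a shift of 374.5 if the mean term is wrong too), but the tests are unchanged. This assumes the standard Kendall formula and equal scan lengths.
- **Series cut to 60 volumes:** 240 of 300 timepoints are lost and the within-scan SD of W rises about √5-fold, under the simulation's assumptions.

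The documents do not support the claim that the primary comparison is already biased or underpowered because of this number. They do support correcting it and checking the code.

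**What to change.** In ReHo Analysis, replace the value 60 by a definition: n is the number of volumes retained after preprocessing (300 less any discarded initial volumes), the same for both scans of every participant. The equal-length condition keeps W comparable between visits and groups.

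Before any ReHo map is analysed, check that the MATLAB program neither contains a fixed 60 nor shortens the series. A simple test is that every W lies between 0 and 1 and that the length of the ranked series equals the retained volume count. If a 60-volume segment is truly intended, state which volumes are used and why.

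The cost is one number in the text and a short code check. The abstract reports that no data analysis had been performed, so on that account the choice can still be fixed without reference to results.
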